
#### Secondary Outcome Measures

The secondary outcome will focus on the long-term effects of repetitive treatments on drug-cue-induced response. Evaluations introduced in primary outcome will also be collected in the follow-up test (T4). Furthermore, self-reported craving in VAS as a subjective indicator for cue-induced drug craving, physiological parameter (cue-induced heart rate) and possible co-variables corresponding to substance-taking history, emotional and mental state will be measured with the clinical diagnosis and psychological questionnaires at baseline (T0), post-test (T3) and follow-up test (T4) respectively.

***VAS*** embedded in VR scenes is a 100-point visual analog scale ranging from 0 (no craving) to 100 (high craving) for self-reported craving. Each patient will be directed to evaluate their current craving at a black screen on one wall of a virtual room. They will be guided to focus on their momentary feeling to make an assessment. The VAS points at baseline (T0) will be compared with the post-test after the last treatment (T3) to identify an expected reduction in self-evaluated craving. The median, range, average and standard deviation of VAS will be calculated for analysis.

***Electrocardiography (ECG)*** Given the association of MA with autonomic nervous system dysfunction (74) and the significant difference in heart rate between drug-cue and neutral-cue in the cue-induced craving paradigm (75), ECG (BIOPAC ECG module, with sampling rate of 1,000 Hz) will be recorded in this experiment as an indicator of physiological changes. In addition, changes in the heart rate interval can reflect abnormalities of autonomic nervous function (76). In addition, its activities are related to executive functions such as working memory, attention maintenance, and response inhibition involved in prefrontal cortex activities (77). In MA studies, it shows significantly reduced heart rate variability in MA populations (76), and the difference between drug-cue and neutral-cue is significantly associated with subjective cravings (78). Therefore, ECG will be recorded at the same time with EEG.

***Anxiety*** as a specific unpleasant emotional state has been observed as a common psychiatric comorbidity in addicts (79). Each patient will be required to complete the Self-Rating Anxiety Scale (SAS) at T0, T3 and T4 (80). The questionnaire consists of 20 items rated on a 1-4 points scale, with a total score ranging from 20 (mild anxiety) to 80 (severe anxiety). The SAS has adequate internal consistency alpha coefficients (α > 0.7). It is a widely used measurement of anxiety levels both in research and in clinical practices.

***Depression*** is another common emotional state exhibited following intense drug craving (79). It will be assessed at T0, T3 and T4 with Self-Rating Depression Scale (SDS) (81). The questionnaire consists of 20 items rated on a 1-4 points scale, with a total score ranging from 20 (mild depression) to 80 (severe depression). The SDS has satisfactory alpha coefficients (α > 0.7) and it has been implemented widely in clinic trials.

***Mood State*** will be evaluated at T0, T3 and T4 with the Profile of Mood States -short form (POMS-SF) (82). The self-reported scale includes 40-items to identify the extent of feeling in respective mood state. The POMS-SF is indicated for current emotional state on a 5-point scale (1 = “very slightly or not at all” to 5 = “extremely”). It is widely used for clinical practice in China (83) and its accessibility and consistent reliability coefficients have been identified among Chinese (with *Cronbach's* α > *0.7*).

### Participant Timeline

All participants will be introduced to follow the schedule of baseline phase, treatment sessions and follow-up test. All patients passing the screening process will enter the treatment procedure. Participants will be grouped into A, B or C to receive MA-VR retrieval combined active TBS (MA VR-active TBS) or MA-VR retrieval combined sham TBS (MA VR-sham TBS) or neutral-VR retrieval combined active TBS (neutral VR-active TBS), respectively. The treatment includes two TMS intervention sessions within 1 week. Each session takes about 30 to 40 min including preparation time, VR retrieval of 3 min, relaxation of 10 min and continuous TBS of 5 min. The post-test will be conducted 1 to 4 days after the last session and the follow-up test will be taken over at least 1 month later. The timeline for participants in this trial is illustrated in Figure 2.

### Sample Size

According to Hanlon et al. (28) study, 25 cocaine users either receiving active- or sham- pre/post TBS treatment showed a significant difference in the reduction of cue craving (*F*_1, 96_ = 5.65, *P* = 0.02). The effect size (*f*= 0.2496) calculated by formula $r^{2}=\frac{df1^{*}F}{df1^{*}F\;+\;df2},f=\sqrt{\frac{r^{2}}{{1-r}^{2}}}$, the 3 (between factor: MA VR-active TBS vs. MA VR-sham TBS vs. neutral VR-active TBS) × 4 (within factor: four repetitive tests) design of the current protocol, the proposed alpha error (α = 0.05) and power (β = 0.95) will be used as the parameters for a prior sample size calculation (in G.Power 3.1). The required sample size is 45 in terms of repeated measures ANOVA with within × between interaction effect.

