**Methods:**

This is a randomized, double-blind, sham-controlled, parallel group trial, targeting participants with MA use disorder aged from 18 to 45 years old. Forty-five eligible volunteers in Shanxi Drug Rehabilitation Center will be recruited and be randomly allocated into three parallel groups, receiving either 1) MA-related cues retrieval in VR combined with active TMS (MA VR scene + TBS) or 2) sham TMS (MA VR scene + sham TBS), or 3) neutral cues retrieval in VR combined with active TMS (neutral VR scene + TBS). Two sessions of post-VR-retrieval TBS will be scheduled on two separate days within 1 week. The primary outcome will detect the memory-related activity by the electroencephalography (EEG) reactivity to drug cues in VR scenes. Secondary outcomes are the self-reported MA craving in VR scene, the physiological parameter (cue-induced heart rate) and the scores of psychological questionnaires including anxiety, depression, and mood. All primary and secondary outcomes will be assessed at baseline, 1-week, and 1-month post-intervention. Assessments will be compared between the groups of 1) MA VR scene + TBS, 2) MA VR scene + sham TBS and 3) neutral VR scene + TBS.

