### Outcome Measures

#### Primary Outcome Measure

We will evaluate the short-term effects of Retrieval-TBS treatment in the reduction of cue-induced drug craving and cue reactivity by comparing EEG in VR scene between baseline (T0) and post-test (T3).

***EEG*** will be recorded by a portable EEG system (Muse by Interaxon Inc.) during each VR session (3 min/scene × 1 MA-related VR scene and 1 neutral-related VR scene = 6 min) at T0 and T3, respectively. Each patient will wear an EEG headset before entering the VR scenes. Four channels (refer to EEG 10-20 system: FP1, FP2, TP9, TP10) and an original reference (FPz) will be retained to measure the brainwave spectrum including delta, theta, alpha, beta and gamma (with a sample rate of 256 Hz and 12 bit resolution), frequency bands between 45 and 60 Hz were omitted because muse hardware applied notch filters at 50 and 60 Hz to reduce environmental noise (67). According to a previous study, there was a significant difference between drug-cue and neutral-cue-induced EEG activities (68). In terms of drug-cue related memory, the frontal theta activity used as a feedback signal in adaptive regulation was highlighted for memory updating (69), which has been suggested as an indicator of the enhanced binding of incoming interconnected information in memory formation (70), while the beta activity which reflects a memory promoting state (70) indicated the level of memory integration in reconsolidation (71). Since the wearable devices available in VR have been applied to classify emotional states (72), we plan to use wearable EEG combined with VR scenes to observe the brain activity associated with memory in the current study. The average power in EEG frequency bands (i.e., δ = 1–4 Hz, θ = 4–8 Hz, α = 8–13 Hz, β = 13–30 Hz, γ = 30–50 Hz) are real-time computed in hardware and sent alongside an indicator of data quality from each sensor. The Muse manufacturer provided on-device computed FFTs (https://sites.google.com/a/interaxon.ca/muse-developer-site/museio) were used to estimate the spectral power density (μV2/Hz) for frontal electrodes in each frequency band in this study. EEG spontaneous measures at the frontal sites were calculated, as shown in Figure 2, by 1 min post-dark data minus 1 min pre-dark data in each frequency band in each VR scene. We used state-related EEG to calculate the EEG activities for drug-related craving state in VR, because cue-induced craving is related to a tonic, slowly changing craving state and Muse is a portable device that may not stably acquire EEG activities during walking in VR scene. Previous studies have used “state-related EEG” to compare different EEG activities in different state (56, 72, 73). Because of the non-normal distribution, power density value and ratios were log-normalized. For statistical tests, a two-tailed alpha of 0.05 was used unless explicitly stated otherwise.

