#### Inferential Statistics to Determine the Efficiency of Intervention

The statistical significance (sig) and effect size (ES) will be evaluated for treatment-effects determination either by paired *t*-test and repeated measures ANOVA test [two factors, test time (baseline vs. post-test) and treatment (MA VR scene + TBS vs. MA VR scene + sham TBS vs. neutral VR scene + TBS)] in parametric estimations or Friedman's chi-square and Kendall's W coefficients in non-parametric statistics. These differences between baseline and post-tests will be compared firstly between the three parallel groups for self-reported craving and neurophysiological measures (e.g., EEG and ECG).

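### The stated 95% power at N = 45 does not apply to the planned primary test: f is miscalculated, and the calculation assumes four tests where the analysis has two

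*Protocol article*

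**What the plan says.** **Sample Size** takes F(1,96) = 5.65, P = 0.02, from a study of 25 cocaine users. It converts this to an effect size: "The effect size (*f*= 0.2496) calculated by formula" r² = df1·F/(df1·F + df2), f = √(r²/(1 − r²)). The design entered in G*Power has three groups and "4 (within factor: four repetitive tests) design of the current protocol". On error rates, "the proposed alpha error (α = 0.05) and power (β = 0.95) will be used as the parameters"; the 0.95 is evidently power, although it is labelled β. The result is 45 participants for the within × between interaction. The correlation among repeated measures and the sphericity correction are not given.

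**Primary Outcome Measure** assesses the short-term effect "by comparing EEG in VR scene between baseline (T0) and post-test (T3"). Under Secondary Outcome Measures, T4 is a follow-up for the long-term effect.

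**Inferential Statistics to Determine the Efficiency of Intervention** names a "repeated measures ANOVA test [two factors, test time (baseline vs. post-test) and treatment", with the three arms as treatment levels. Time therefore has two levels.

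**Abstract, Methods** gives three occasions: "All primary and secondary outcomes will be assessed at baseline, 1-week, and 1-month post-intervention". **Study Design** lists T0, T1/T2, T3 and T4.

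**The concern.** The Sample Size section prints its inputs, its formula and its result, and these do not agree. The test that was powered also has a different time factor from the test that is to be run. In this type of calculation the number of repeated measurements enters the noncentrality parameter directly, so moving from four tests to two halves it.

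The 95% figure is the only statistical justification given for the size of the trial. If it does not apply to the primary comparison, readers will misjudge how likely the trial is to detect its own planning effect.

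**Working it through.** **Inputs.** From Sample Size: F = 5.65, df1 = 1, df2 = 96; stated f = 0.2496; k = 3 groups; m = 4 tests; α = 0.05; target power 0.95; N = 45. From Primary Outcome Measure and Inferential Statistics: m = 2. Assumed, because not stated: correlation ρ = 0.5 and sphericity ε = 1, the usual G*Power defaults.

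**Step 1: effect size from the printed formula.**
- r² = 5.65/(5.65 + 96) = 5.65/101.65 = 0.0556
- f = √(r²/(1 − r²)) = √(5.65/96) = 0.2426

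The stated value is 0.2496, a gap that rounding cannot explain. The printed F and degrees of freedom give P = 0.019, which agrees with the printed 0.02, so the inputs are consistent and the slip lies in f.

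**Step 2: reproduce N = 45.** Power comes from the noncentral F distribution with λ = f²·N·m/(1 − ρ), numerator df (k − 1)(m − 1) and denominator df (N − k)(m − 1). With f = 0.2496, m = 4 and N = 45:
- λ = 0.2496² × 45 × 4/0.5 = 22.43, on 6 and 126 df, power 0.955
- at N = 44, power is 0.9498

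So 45 is exactly the minimum, and the plan's figure is reproduced.

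**Step 3: correct the inputs one at a time, N = 45, ρ = 0.5.**

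| f | Time levels | Power at N = 45 | N for 95% |
|---|---|---|---|
| 0.2496 | 4 (as stated) | 0.955 | 45 |
| 0.2426 | 4 | 0.942 | 47 (48 for equal arms) |
| 0.2496 | 2 | 0.832 | 66 |
| 0.2426 | 2 | 0.809 | 69 |
| 0.2426 | 3 (T0, T3, T4) | 0.892 | 56 (57 for equal arms) |

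For the fourth row, λ = 0.2426² × 45 × 2/0.5 = 10.59 on 2 and 42 df.

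Most of the loss comes from the time factor (0.955 to 0.832). The slip in f costs 1 to 2 percentage points.

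**Step 4: sensitivity to the unstated correlation.** The middle column is the 3 × 2 test at N = 45 and f = 0.2426. The last column is the N that the plan's own 3 × 4 calculation (f = 0.2496) would have returned.

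| ρ | Power of the 3 × 2 test | N from the plan's calculation |
|---|---|---|
| 0.3 | 0.658 | 61 |
| 0.4 | 0.730 | 53 |
| 0.5 | 0.809 | 45 |
| 0.6 | 0.892 | 36 |
| 0.7 | 0.961 | 28 |

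With sphericity 1, only ρ = 0.5 in this list returns the published 45.

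**Step 5: effect-size convention.** Two other ways of entering f were tried: λ = f²·(N − k)(m − 1) and λ = f²·N·(m − 1). At m = 4 and f = 0.2496 they need 117 and 114 participants, so neither is what was used. Under the first, the 3 × 2 test at N = 45 and f = 0.2426 has power of only about 0.25. Any restated power therefore has to name its convention.

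**The case against.** The strongest objection is that 81% is conditional. The protocol gives no correlation, and the value that reproduces N = 45 shows what was probably entered in the software, not how strongly frontal EEG power will correlate between T0 and T3. At a correlation of 0.7 the 3 × 2 test would exceed 95%. The result also depends on the effect-size convention. This stands as a limit on the figure: 81% must be quoted with its assumptions. It does not rescue the 95% claim, because a planner assuming 0.7 would have obtained 28 participants from the stated calculation, not 45.

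The four tests may have an innocent origin. Study Design lists four entries if T1/T2 is counted as one, and the timeline figures are not available here. That may explain the number, but no analysis described in the article uses four time levels. The abstract's three occasions support a middle reading, which still gives only 0.89. The mismatch could in principle be resolved from the other side, by changing the time factor in the analysis, but the two-level reading is the one that the primary outcome and the stated ANOVA both support.

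A reader might go further in two ways that the documents do not support:
- **Loss of participants.** One might infer that power falls further because incomplete or contaminated cases are excluded. Data Preparation and Descriptive Statistics describes a validity check against completion and missing-data thresholds, then multiple imputation. It does not say that such cases are dropped, and it gives no number.
- **The borrowed outcome.** One might count the use of a craving effect to plan an EEG endpoint as part of the error. The section openly says that the effect is for craving. That is a planning choice, not a mistake in the arithmetic.

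**Conclusion.** The concern holds. The printed formula gives f = 0.2426, and the powered design (four tests) is not the analysed design (two). The first error rests on no assumption at all. On the plan's own 3 × 4 design it is enough to bring N = 45 just below target, at 0.942.

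For the primary 3 × 2 interaction, power at N = 45 is about 81% with the corrected f. This assumes correlation 0.5, sphericity 1 and the G*Power convention that reproduces the published N. The type II error is then about 19% (1 − 0.809), against the 5% implied.

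A reader might infer that the trial is badly underpowered or must be enlarged. That does not follow: under the settings that reproduce the plan's own N, power remains just above 80%. Nor does the article say how a null EEG result would be interpreted. What fails is the stated 95%.

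**What to change.** In Sample Size:
1. Correct f to 0.2426.
2. Reconcile the number of repeated tests with Primary Outcome Measure and Inferential Statistics. As those sections stand, the primary test is 3 groups × 2 times (T0, T3).
3. Replace the 95% claim with the power of that test at N = 45, stating the assumed correlation, the sphericity value and the effect-size convention. At correlation 0.5 this is about 81%; the range of 0.66 to 0.96 for correlations 0.3 to 0.7 should be shown beside it.

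This rewrites one paragraph and needs no extra participants. The cost is a less favourable stated power.

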### Data Collection and Statistical Methods

The screener will ensure the inclusion and exclusion criteria and collect basic characteristic data before randomization. The outcome evaluators will play an important role in measurements of the primary and secondary outcomes. The data of all participants will be stored in documents and kept in locked boxes by the main investigator to protect personal information. Furthermore, the EEG data will be stored by the primary research on a locked computer with a password.

#### Data Preparation and Descriptive Statistics

After inspecting original data, identifying unusual cases, transforming and summarizing data-sets according to different types of variables: the mean, median, standard deviation, ranges and valid samples will be required at first, as well as the counts and percentages specific for categorical variables. Firstly, running SPSS 21.0 for basic check of validated data both based on the extent of treatment completion (>85%) and accepted level of missing/obscure/contaminated data (<10–20%). The missing data will be estimated via multiple imputations. Secondly, the distribution of data will be analyzed both by stem-and-leaf plot (SPSS 21.0), the actual data calculated for normality overlay a normal curve will be required to determine that to what extent it is a normal distribution (without significance at given alpha = 0.05). For a poor fitted normal curve, non-parametric inferential will be selected, while the standard or similar standard alloy will run the parametric inferential.

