### Participants

Participants with MUD in Shanxi Drug Rehabilitation Center will be voluntarily recruited to this treatment. After initial confirmation, eligible participants will then be required to sign an informed consent. The number and reasons of exclusion individuals, as well as those who reject or withdraw consent will also be recorded. *Inclusion criteria:* Selected participants will have to (1) be clinically diagnosed with Amphetamine-Type Substance Use Disorder according to Diagnostic and Statistical Manual of Mental Disorders (DSM-5) criteria, (2) abstinence periods at least 2 weeks without obvious withdrawal symptoms (e.g., drowsiness and dysphoria), (3) be aged 18 and 45 years old, and be right-handed, (4) be able to speak and read Chinese, (5) sign a consent form before intervention procedure.

*Non-inclusion criteria:* Participants meeting at least one of the following criteria will not be enrolled in this study: (1) meeting the diagnostic criteria of any other psychiatric disorder under DSM-5; (2) using other kinds of drugs (e.g., heroin, cocaine) in the past 30 days; (3) having contraindications to TMS treatment (head trauma, epilepsy or the history of epilepsy, metal implant, pregnancy and so on); (4) having a history of mental illness or a family history of mental illness; (5) be insensitive to VR scene (identified at the baseline); (6) having received psycho-therapy or TMS intervention in the last 6 months; (7) receiving medication treatment recently; (8) illiteracy; (9) having visual or hearing problems; (10) the individual threshold of TMS was higher than 50% of the maximum output of the TMS equipment; (11) scheduled to receive psycho-therapy or medication treatment for the next 2 months. *Exit criteria:* Participants will be allowed to withdraw from the clinical trial if they (1) voluntarily wish to stop the TBS sessions; (2) can hardly tolerate any aversive reactions (e.g., itching, numbing) or have a desire for other treatments; (3) do not complete the TBS sessions for other reasons; (4) suffer from worsening symptoms such as enhanced craving.

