### Intervention

The “VR retrieval–TBS” intervention will be given twice within 1 week. Each intervention session contains a MA-related VR scene to retrieve memory (or a neutral VR scene in a control group), a 5-min TBS treatment, and a 10-min interval in between them to conform with the suggestion that a 10-min reconsolidation window may improve the effectiveness of the subsequent intervention (8, 57). A short TBS trial will be delivered before the full-length treatment to decrease risks and improve clinical adherence. The pulse intensity of TBS will be assigned according to identified individual resting motor threshold (RMT).

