##### TBS Pattern

The cTBS will be applied to reduce activation of the OFC circuit. TBS sessions will be carried out with a hand-held figure-of-eight coil with the size of 90 mm diameter of one half of the “8” shape (B9076, Yiruide Co., Wuhan, China), attached to a YRD CCY-I stimulator (Yiruide Co., Wuhan, China). Following a 10-min rest after memory retrieval, participants either in the MA VR scene + TBS group (*n* = 15) or in the MA VR scene + sham TBS group (*n* = 15) or in the neutral VR scene + TBS group (*n* = 15) will receive two TBS sessions within 1 week. In each session, all participants will receive two 1,800-pulse trains of cTBS in 5 min (three pulses are given at 50 Hz as one burst; a burst will be given every 200 s as 5 Hz; one train for 120s, containing 1,800 pulses) with a pulse intensity of 80% of RMT following Hanlon et al. (62)'s suggestion. A 60-s break will give to participants after the first train (1,800 pulses). The choice of TBS intensity will consider the participants' real-time feedback and health condition to TMS stimuli. If a participant reported unbearable discomfort with TBS stimulation, we will turn down the intensity gradually until acceptable. If a participant still reported unbearable discomfort when the stimulation intensity was lower than 60% of the RMT, this participant will withdraw from the experiment. These parameters have been applied by previous studies (62) and proposed in safety guidelines (63).

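### The 85% treatment-completion screen, if applied to each participant, keeps only full completers and risks post-randomisation selection bias of unknown direction

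*Protocol article*

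**What the plan says.** Under Data Preparation and Descriptive Statistics, the first step in SPSS is a basic check of validated data, "based on the extent of treatment completion (>85%) and accepted level of missing/obscure/contaminated data (<10–20" per cent). The next sentence says that missing data will be multiply imputed. The article does not say whether 85% applies to each participant or to the whole dataset, and it does not say in words that anyone below it is dropped. It nowhere states that all randomised participants will be analysed in their assigned group.

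On the amount of treatment, the Intervention section says that the "intervention will be given twice within 1 week", and TBS Pattern says that in each session "all participants will receive two 1,800-pulse trains of cTBS in 5 min".

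On stopping, the exit criteria under Participants are permissive: "Participants will be allowed to withdraw from the clinical trial if they" meet one of several conditions. These include that they "can hardly tolerate any aversive reactions", that they "do not complete the TBS sessions for other reasons", or that they "suffer from worsening symptoms such as enhanced craving". TBS Pattern is mandatory: if discomfort remains unbearable below 60% of resting motor threshold, "this participant will withdraw from the experiment". Identification Method and Management System describes a similar situation (persistent or intolerable pain) but says only that treatment is not continued.

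The sample size of 45 appears in the Abstract as the number to be recruited and in Sample Size as the number required.

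**The concern.** A completion criterion depends on what happened after randomisation. When it decides who enters the analysis, the groups compared are no longer the groups that were randomised. This matters most when the reasons for stopping are tied to the outcome or the treatment, and both apply here. Worsening craving is an exit reason, and self-reported craving is a secondary outcome that is among the first measures compared between groups. Intolerance of stimulation is also an exit reason, and its frequency may depend on the coil used.

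Imputation would not clearly repair this. The completion check comes first in the text and imputation follows, so on a natural reading those screened out are not imputed. Someone withdrawn from the experiment, rather than only from stimulation, may also have no T3 or T4 data.

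The data-quality limit is a second weak point. It is a range, so a recording with 15% contaminated data could be kept or dropped at discretion. That bears on the EEG primary outcome, since the article itself notes that the portable device may not record stably while participants walk in the VR scene.

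With 15 per group, two or three people are enough to move a group mean noticeably.

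**Working it through.** **1. What more than 85% means.** Inputs: two sessions (Intervention) and two trains per session (TBS Pattern), so four trains in all.

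- By session, possible completion is 0/2, 1/2 or 2/2, that is 0, 50 or 100%.
- By train, it is 0, 25, 50, 75 or 100%.

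On either count only 100% exceeds 85%. A per-participant rule is therefore a completers-only rule.

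**2. Size and direction of the possible bias.** The article gives no dropout figures, so these are illustrative assumptions: 15 per group, no true effect, normally distributed craving change in SD units with higher meaning worse, and those who leave being exactly the worst responders in their group.

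If the top k of 15 leave, the expected mean of the rest is minus the sum of the k largest expected normal order statistics, divided by (15 − k). For n = 15 the three largest are 1.736, 1.248 and 0.948.

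- k = 1: −1.736/14 = −0.12
- k = 2: −(1.736 + 1.248)/13 = −0.23
- k = 3: −(1.736 + 1.248 + 0.948)/12 = −0.33

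The large-sample approximation, −φ(z)/(1 − q) with q = k/15, gives −0.14, −0.25 and −0.35, slightly too large for groups of 15.

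Bias in the active-minus-sham difference (negative favours active):

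| Exits, active / sham | Bias, SD |
|---|---|
| 2 / 2 | 0 |
| 3 / 1 | −0.33 + 0.12, about −0.20 |
| 1 / 3 | about +0.20 |
| 3 / 0 | −0.33 |
| 0 / 3 | +0.33 |

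The approximation gives ∓0.21 for the 3-versus-1 cases, the same to one decimal. If leaving correlates only 0.5 with the outcome, the 3-versus-1 figure halves to about 0.1 SD.

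**3. Allowance for loss.** First the plan's own figure. Inputs from Sample Size: f = 0.2496 (as printed), alpha 0.05, power 0.95, three groups, four measurements, within-between interaction. The correlation between repeated measures (ρ) and the sphericity correction are not given; I assumed 0.5 and 1.

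- λ = f²·N·m/(1 − ρ) = 0.0623 × 45 × 4/0.5 = 22.43
- df1 = (3 − 1)(4 − 1) = 6
- df2 = (45 − 3)(4 − 1) = 126
- Power = 0.955

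Forty-five is the smallest N that reaches 0.95, so the plan's figure is reproduced. It depends on ρ: the required N would be 86 at ρ = 0, 61 at 0.3 and 28 at 0.7.

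On the same inputs with ρ = 0.5, power is 0.938 at N = 42, 0.917 at 39 and 0.888 at 36. Since 45 is both required and recruited, any exclusion takes power below the target.

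**The case against.** The strongest reply is that the text describes a basic check, not an exclusion. It does not set the level at which 85% applies, and imputation in the next sentence could cover everyone. This is a condensed article, and the full protocol or a SAP may define the analysis sets. Part of that stands: exclusion is the natural reading, not an explicit rule. But a criterion based on treatment received is already stated here, ahead of imputation, and nothing in the article balances it with an all-randomised analysis. That is more than an omitted detail.

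A reader might go further and infer that the rule tilts the result towards active TBS. The document does not support this. The craving exit applies to every group and would be commoner under sham if TBS works, which would flatter sham. Sham also stimulates the scalp skin and superficial muscles, and nothing says that discomfort will be commoner under active TBS. Exits for intolerance favour active TBS only if those people would have done worse, which is not shown. Two of the three groups receive active TBS, so an active-versus-sham mechanism says nothing about the contrast between MA and neutral retrieval.

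A reader might also infer that the exit rules remove people whose craving rises. The exit criteria only allow them to leave. Withdrawal is required only for persistent discomfort, after intensity has been lowered in steps, and a short trial stimulation is given first to help adherence.

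Finally, data analysts are to be blinded, which limits choosing the data-quality cut in favour of a group. The blinding is, however, described as applying during treatment sessions.

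**Conclusion.** The point holds as a risk of post-randomisation selection bias of unknown direction. If the completion check is applied to each participant, only people who received all the treatment qualify, and the reasons for stopping are plausibly related to outcome or treatment.

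For craving change the bias is zero with equal exits of this kind and roughly 0.2 SD either way for a 3-versus-1 imbalance. That figure assumes that those leaving are the worst responders, which is an upper case for such an imbalance. The exit counts are illustrations, not predictions. For the EEG primary outcome the link from craving-related exit is indirect and I have not quantified it. The loss of power is modest, but it starts with the first exclusions because the sample size has no margin.

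**What to change.** - Make the primary analysis all randomised participants in their assigned group, whatever number of sessions they completed, with multiple imputation carried out within that set.
- Use the set with more than 85% completion only as a sensitivity analysis, and state that the threshold applies to each participant and means both sessions in full.
- Replace the 10–20% range with a single EEG-quality cut-off, fixed in advance and applied blind to group.
- Seek the T3 and T4 assessments, which are already scheduled, from participants who stop TBS and still consent.
- Reconcile TBS Pattern, which withdraws the participant from the experiment, with Identification Method and Management System, which says only that treatment is not continued. Which rule should apply is for the investigators to settle.

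Most of this is analysis wording. Continued assessment after stopping also touches a participant rule, so it is somewhat more than an analysis edit, but it adds no new visits. The small downside is that including people who received less treatment may slightly dilute the estimate. The changes should be made before any data are screened or unblinded, because later they would not be credible.
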